### Third phase: a randomized field trial study

#### Participants and setting

This parallel-group, double-blind, controlled, randomized field trial, superiority framework with an allocation ratio of 1:1 will be conducted on infertile couples who underwent infertility treatment in Isfahan Fertility and Infertility Center, Isfahan, Iran. Couples, at least one of whom suffers from mild to moderate depression, will be invited to participate in the quasi-experimental study. The inclusion criteria will include no history of severe mental disorders and no stressful event during the last 3 months. The exclusion criteria will be a stressful event or the onset of assisted reproductive treatment during the intervention and ovarian hyper-stimulation syndrome due to ovarian induction.

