#### Recruitment

Couple’s eligibility assessment and screening will be performed by the Ph.D. candidate in reproductive health. During the first interview, X infertile couples will be invited, and the levels of depression, anxiety, stress, and infertility adjustment will be evaluated using validated questionnaires. After determining the eligible couples, X couples will be randomly selected and invited by the researcher to participate in the study. The study objectives and the way of participating in the study will be explained to couples who accept the invitation.

The informed consent will be obtained from eligible couples by a legal advisor in the infertility center. The representative of the Ethics Committee of the Isfahan University of Medical Sciences will supervise all stages of the research and will decide to end the trial.

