#### Sampling and data collection

After determining the eligible couples, X couples will be randomly selected by the researcher. To randomly assign the couples to the intervention and control groups, X closed envelopes containing blue and green cards will be prepared. The couples will be referred to the midwife consultant and receive one of the envelopes and complete demographic characteristics.

The midwife and participants will be blinded to the study group. After random allocation, one researcher, who will not be involved in sampling and random allocation, will assign each group’s card color. Couples’ depression, anxiety, stress, and infertility adjustment levels will be evaluated using valid questionnaires 2 and 3 months after starting the intervention and compared between the groups (Table 1).

**Table 1 Tab1:** Schedule for data collection during the trial

Time point	Study period				
	Enrollment	Allocation	Post allocation		Closeout
	Pre-baseline	Baseline	Time 1	Time 2	
Enrollment					
Eligibility screen	X				
Informed consent	X				
Allocation		X			
Participant characteristics					
Demographics		X			
Infertility profile		X			
Interventions					
Couple-based coping strategies		X			
Solution-oriented counseling		X			
Outcomes assessment					
Depression			X	X	X
Anxiety			X	X	X
Stress			X	X	X
Infertility adjustment			X	X	X

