#### Intervention

The intervention will begin before starting medical treatment. The counselors will be MSc holders in psychological counseling. They will be trained in the developed couple-based coping strategies using face-to-face education and a role modeling approach.

For the intervention group, a counseling psychologist will be educated on the developed couple-based coping strategies based on the color chosen for one group (intervention group) and solution-oriented counseling for the other group (control group).

The number, duration, and intervals of the sessions for intervention and other educational intervention (control) groups will be set identically. It is estimated that the counseling program will be scheduled 3 to 5 times once or twice each week. The researchers will bear the intervention and transportation costs for both intervention and control groups. Participants should not participate in any other research during the intervention. The research is expected to proceed without any harm; however, in case of harm, the main researcher will be responsible for compensating for the reparable harm.

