#### Outcomes

The outcome will be the mean score of depression, anxiety, stress, and infertility adjustment and the magnitude of their change on enrollment and 3 months after starting the intervention in couples in the intervention group compared with those in another educational intervention (as the control group).

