#### Data collection tools

Data will be collected using a self-report 21-item Depression Anxiety Stress Scale (DASS-21) and a revised version of the Fertility Adjustment Scale (R-FAS) [20]. Each of the DASS-21 subscales contains seven items on a 4-point Likert scale (0–3) from 0 (not at all true for me), 1 (to some extent true for me), 2 (considerably true for me), to 3 (absolutely true for me). A higher score indicates greater depression, anxiety, and stress.

Adjustment to infertility will be assessed using the self-report R-FAS, including 12 items on a 6-point Likert scale (1–6) from 1 (strongly disagree) to 6 (strongly agree). The final score will be obtained by summing the scores of questions; a higher score indicates a lower adjustment toward infertility.

To promote participant retention and complete follow-up, prior to each counseling session, the researcher will encourage couples who discontinue or deviate from intervention protocol to participate in counseling sessions through a telephone call. Missed data will be completed by the researcher through a telephone call and questions. Data monitoring in all phases will be done by the principal investigator.

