#### Data management and analysis

Data will be analyzed using the SPSS 19 software and statistical tests, including the independent *t*-test, pair *t*-test, chi-square, and repeated measures analysis of variance (RM ANOVA). If the measurements at the enrollment phase appear differently in the groups, analysis of covariance (ANCOVA), controlling for baseline data and independent variables (group as a fixed parameter and enrollment mean scores as a covariate), will be used. Also, the baseline value of outcome variables and potential confounding variables which are different between the two groups will be adjusted to avoid potential risk of bias and detect independent results. The data normality will be evaluated through the Kolmogorov-Smirnov test. If the data are not normally distributed, nonparametric tests such as Wilcoxon will be used. In the case of missing data, we will utilize the last value carried forward method to impute missing values.

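### Last value carried forward, the only missing-data rule, gives anyone without a 2-month score a 3-month change of zero and can bias the comparison between arms

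*Protocol article*

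**What the plan says.** The third-phase section *Data management and analysis* ends with the missing-data rule: "In the case of missing data, we will utilize the last value carried forward method to impute missing values". It attaches no condition and names no alternative. The tests listed there are t-tests, chi-square and repeated measures ANOVA, with ANCOVA if the groups differ at enrolment.

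The rule is a second step. Under *Data collection tools* the article first says: "Missed data will be completed by the researcher through a telephone call and questions". Carrying forward applies to what is still missing after that.

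The schedule comes from four other sections:
- *Recruitment*: at the first interview, "the levels of depression, anxiety, stress, and infertility adjustment will be evaluated using validated questionnaires". This is the only measurement before the intervention that the text describes.
- *Intervention*: it is estimated that "the counseling program will be scheduled 3 to 5 times once or twice each week".
- *Sampling and data collection*: outcomes "will be evaluated using valid questionnaires 2 and 3 months after starting the intervention".
- *Outcomes*: the comparison uses the mean scores and "the magnitude of their change on enrollment and 3 months after starting the intervention".

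On who enters, *Participants and setting* (third phase) says: "Couples, at least one of whom suffers from mild to moderate depression, will be invited to participate".

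**The concern.** Carrying the last value forward assumes that nothing changes after a person's last measurement. Here the gap can be long: no score is scheduled between enrolment and month 2, so a person lost in that interval has only the enrolment score, and the computed 3-month change is exactly zero.

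That assumption fits this trial poorly. Where a partner was selected on a depression score, that score may fall through regression to the mean in either arm. The control arm also receives counselling, so it may improve as well. Setting some participants' change to zero pulls each arm's mean change towards zero by an amount that depends on how many were lost in that arm. What is at stake is the 3-month between-group comparison, which is the trial's stated outcome. The direction of the error cannot be known in advance, so the rule cannot be defended as reliably conservative.

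**Working it through.** The protocol gives no sample size (it is printed as X), power, SD, effect size or drop-out rate. There is no figure to reproduce, and every numerical input below is an assumption.

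**Step 1: which value is carried.** At one session a week, 5 sessions take about 5 weeks, which is the longest course described. It ends before the 2-month assessment. A person lost during counselling, or at any time before month 2, carries the enrolment score. A person lost between months 2 and 3 carries the 2-month score.

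**Step 2: formula.** Assume that drop-out is unrelated to outcome. Let μ be the mean 3-month change in an arm (I = intervention, C = control), d the proportion lost, f the share of drop-outs with only an enrolment score, and g the share of the 3-month change already reached by month 2. Then

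estimated difference = μ_I(1 − d_I·h) − μ_C(1 − d_C·h), with h = f + (1 − f)(1 − g).

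**Step 3: no true effect, in DASS-21 points.** With a common fall c and f = 1 (so h = 1), the estimate is c(d_I − d_C). For 10% lost in the intervention arm and 25% in the control arm:
- c = 3: 3 × (0.10 − 0.25) = −0.45
- c = 5: 5 × (0.10 − 0.25) = −0.75

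This falsely favours the intervention. With the losses swapped between arms, the error has the same size in the other direction. A subscale of seven items scored 0 to 3 runs from 0 to 21.

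**Step 4: true difference of −0.50 SD** (μ_I = −1.0, μ_C = −0.5, g = 0.8):

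| Loss I / C | All carry enrolment (f = 1) | Half do (f = 0.5) | None do (f = 0) |
|---|---|---|---|
| 10% / 10% | −0.45 | −0.47 | −0.49 |
| 20% / 20% | −0.40 | −0.44 | −0.48 |
| 30% / 30% | −0.35 | −0.41 | −0.47 |
| 30% / 10% | −0.25 | −0.35 | −0.45 |
| 10% / 30% | −0.55 | −0.53 | −0.51 |

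Example: at 20% / 20% with f = 1, −1.0 × 0.80 + 0.5 × 0.80 = −0.40, which is 80% of the true value.

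The pull can also go the other way under equal loss. If the effect wanes after month 2, then g exceeds 1 and h is negative when f = 0. With g = 1.4 and 20% loss, −0.50 × (1 + 0.20 × 0.4) = −0.54.

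**Step 5: simulation of error rates and standard errors.** Independent t-test on 3-month scores; 4,000 runs; 50 or 100 per arm; correlation 0.5 with enrolment and 0.7 between months 2 and 3; drop-out unrelated to outcome; individuals treated as independent.
- No true effect (both arms −1.0 SD), 10% vs 30% lost, f = 1: false difference 0.20 SD. Rejection is about 15% with 50 per arm and 26% to 27% with 100. Coverage of the 95% interval is about 85% and 74%.
- Milder case, no true effect, 10% vs 20% lost, f = 0.5: the formula gives a difference of 0.06 SD in size. Rejection is 6.2% and 6.5%.
- No true effect, equal 20% loss, f = 1: no bias, rejection 4.7% and 5.2%.
- True −0.50, equal 20% loss, f = 1, 50 per arm: reported standard error 0.209, actual sampling SD of the estimate 0.208, coverage 92.5%. The standard error from observed 3-month data only is 0.223.

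**The case against.** The strongest reply is that the protocol limits the problem before the rule applies. Couples who discontinue are telephoned, and missed data are completed by telephone, so leaving counselling need not mean having no outcome score. The two arms have the same number, length and spacing of sessions, and costs are covered in both, which works against unequal loss. If most of those lost have a 2-month score, Step 4 shows a negligible bias. This stands as a limit on size. It does not remove the point, because the carry-forward rule exists for whatever the telephone calls fail to recover.

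A second reply is that a statistical analysis plan may settle the matter. It would count if the article were silent, but the article names one method without qualification.

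Three stronger readings are tempting, and the documents do not support them:
- *Standard errors are always too small.* A reader might infer this because filled-in values count as observed. The reported standard error is indeed below that from observed data only (0.209 against 0.223), but it matched the estimate's own sampling variation. Type I error stayed near 5% when loss was equal and there was no effect. The loss of coverage comes mainly from bias.
- *Equal drop-out always shrinks the effect.* This needs enrolment scores to be carried, or an effect still growing after month 2. A waning effect is exaggerated.
- *Drop-outs will often carry the screening score.* The schedule makes this possible, but no drop-out timing is stated. Table 1 marks outcomes at Time 1, Time 2 and closeout without dates, so even the first follow-up is dated only in the text.

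Two further limits apply. Only one partner has to be depressed, so the other partner's score, and everyone's anxiety, stress and adjustment scores, are not directly selected to be high. Nor does the article state that control scores are expected to fall.

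**Conclusion.** The concern holds as a bias problem with a stated rule. As the sole method for residual missing data, carrying the last value forward gives participants without a 2-month score a change of zero. That distorts the 3-month comparison when losses or changes differ by arm.

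Under the assumptions in Steps 3 and 4, the error is a false 0.45 to 0.75 points with 10% vs 25% early loss and no effect, or retention of about 80% of a true difference with equal 20% early loss. Both figures take every drop-out to be lost before any follow-up, so they are unfavourable cases; with 2-month scores close to the 3-month level the bias nearly vanishes. Attrition is left to the pilot, so the real size cannot be stated. The point is worth correcting because a better method can use scores that the trial already collects. It does not show that the trial's result will be materially wrong.

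**What to change.** In the third-phase *Data management and analysis* section, replace last value carried forward with one of the following:
- a likelihood-based mixed model for repeated measures on all observed enrolment, 2-month and 3-month scores, with group, time and group by time, and couple as a cluster. This takes the place of repeated measures ANOVA on imputed data, and the 3-month group contrast is read from it;
- multiple imputation by arm, using enrolment, 2-month and partner scores.

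Both assume that data are missing at random given the scores used. Add one sensitivity analysis that shifts missing intervention-arm scores in the unfavourable direction. Keep the telephone completion as the first step.

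Cost: no extra visits or participants. Confidence intervals will be slightly wider than under the present rule, and some extra programming is needed. The mixed model is not among the methods now listed, so choosing it changes the main analysis as well as the missing-data sentence.

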### Presentation of the results

All results of the trial without any restrictions will be published.

## Discussion

Given that coping strategies have dissimilar effects on infertile couples’ mental health, appropriate coping strategies need to be taught to promote their mental health. A study has indicated that strategies used by infertile couples are influenced by cultural and social values and norms of the society where they live [13]. It has also been emphasized that culture affects the way a particular gender would interpret infertility, the way they would respond to it, and even the strategies they would apply to deal with this issue [21].

Therefore, it is necessary to develop supportive programs in treating couples’ infertility according to their lived experiences facing infertility and their social and cultural context. In addition, the infertility crisis is an event that affects couples’ married life and interactions, management of which requires active and responsible participation of couples. As a result, the interaction between coping strategies of each couple does not increase the psychological burden of infertility on the other.

In an effort to provide psychological support to infertile couples, Zurlo has developed a model of mental health predictor variables in infertile couples undergoing treatment that demonstrates the importance of adaptive coping strategies for infertile couples’ mental health [22]. The effect of some counseling methods on coping strategies of couples undergoing assisted reproductive technology has also been evaluated. Rasoulzadeh Bidgoli reported that the use of the Collaborative Infertility Counseling Model was associated with an increase in adaptive coping strategies such as seeking social support and problem-focused coping strategies in women undergoing infertility treatment [23].

In a study by Czamanski et al., positive reappraisal coping intervention and problem-solving skills training in women awaiting assisted reproductive technology resulted in increased use of problem-focused strategy and decreased use of emotion-focused strategy [24].

One study evaluated the effect of Positive Adjustment Coping Intervention using a smartphone to provide psychological support to women undergoing infertility treatment and found that the program was associated with a reduction in women’s psychological burden during treatment [25]. Moreover, the positive effect of cognitive-behavioral interventions on stress reduction in women undergoing assisted reproductive technology has been reported [24]. These findings suggest that adaptive coping strategies can reduce the psychological burden of infertility. Therefore, it is necessary for the couple-based strategies developed in this study to focus on the interaction between couples in order to reduce the psychological burden resulting from infertility and treatment in couples undergoing the treatment.

In the present study, coping strategies used by infertile couples to interact with each other and improve their adjustment to infertility will be extracted by analyzing their lived experiences and evaluating their emotions and feelings toward infertility. Such strategies, extracted and designed based on society’s cultural and social contexts, will better meet the couples’ emotional needs compared to other strategies. When a strategy is used by a partner regardless of the other partner’s emotional and strategic needs, it may harm another partner’s mental health. Therefore, designing couple-based coping strategies based on the data of a qualitative study and the cultural conditions of society is expected to minimize the possible friction between strategies used by couples and improve their relationships.

## Data Availability

The datasets will be available from the corresponding author upon reasonable request.

## Abbreviations

DASS-21: 21-item Depression Anxiety Stress Scale
R-FAS: Revised Version of the Fertility Adjustment Scale
